### 3.1 Dose limiting toxicity (DLT)

Dose limiting toxicity (DLT) is evaluated within 42 days after administration of RRG-003 according to Common Terminology Criteria for Adverse Events, NCI-CTCAE V5.0. DLT is defined as hematologic toxicity  $\geq$  grade 4, nonhematologic toxicity  $\geq$  grade 3, or aural toxicity in grade 2 or 3 within 6 weeks. Aural toxicity was listed as follow:

| Adverse Events               | Grade 2 ear adverse events                                                                                  | Grade 3 ear adverse events                                                                              |
|------------------------------|-------------------------------------------------------------------------------------------------------------|---------------------------------------------------------------------------------------------------------|
| Ear pain                     | Moderate pain; limiting instrumental Activities of Daily Living (ADL)                                       | Severe pain; limiting self care ADL                                                                     |
| External ear pain            | Moderate pain; limiting instrumental ADL                                                                    | Severe pain; limiting self care ADL                                                                     |
| Hearing impaired (Pediatric) | Pediatric (on a 1, 2, 3, 4, 6, and 8 kHz audiogram):
Threshold shift >20 dB at 4 kHz in at least one ear | Pediatric (on a 1, 2, 3, 4, 6, and 8 kHz audiogram):
Hearing loss sufficient to indicate therapeutic |

|                                                |                                                                                                                                 |                                                                                                                                                                                                         |
|------------------------------------------------|---------------------------------------------------------------------------------------------------------------------------------|---------------------------------------------------------------------------------------------------------------------------------------------------------------------------------------------------------|

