#### 4. Subject inclusion criteria, exclusion criteria, and suspension criteria

##### 4.1 Inclusion Criteria

8. Participants and their guardians can fully understand and voluntarily sign the informed consent of this study, willing to cooperate with follow-up at the specified time points in the trial.
9. Be able to communicate well with the researchers and comply with the requirements under the help of the guardian. For young children without mature language skills, they could cooperate and comply with the requirements under the help of guardians.
10. A proper understanding of the trial and an appropriate expectation of the benefit.
11. 1-18 years old, gender is not limited.
12. A diagnosis of DFNB9 congenital deafness was determined based on the clinical symptoms, and gene mutation analysis for the presence of either *OTOF* homozygous or bi-allelic mutations in *OTOF*.
13. Audiology inclusion criteria: Severe to complete hearing loss ( $\geq 65$  dB).
14. Satisfy the requirements for otological surgery: conditions such as middle-inner ear deformity, vestibular-cochlear nerve development abnormality, and ear inflammation, etc. are excluded through CT scan and/or MRI scan within 3 months or during screening.

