### 7.2 Tolerability and safety observation indicators

7.2.1 Vital signs: heart rate, respiration, body temperature, blood pressure;

7.2.2 Physical examination: major organs and systems;

7.2.3 Neurological examination: MRI;

7.2.4 Laboratory tests: blood biochemistry, coagulation function, blood and urine routine, anti-AAV

neutralizing antibody, ELISpot, blood qPCR for AAV shedding detection;

7.2.5 Electrocardiography: standard 12-lead ECG;

7.2.6 Imaging examination: CT or MRI;

7.2.7 Specialist medical examination: external ear and ear canal, tympanic membrane, tympanic chamber, mastoid process

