#### 13.8.2 Treatment Precautions

In accordance with the regulations of NMPA's new GCP, patients who are ready to participate in the trial will be screened strictly according to the inclusion and exclusion criteria, avoiding to include patients who do not meet the criteria in the trial. To guarantee the safety of subjects, risk control will be carried out during the trial and is planned as follows:

- (1) Multiple follow-up visits will be performed before dosing, during the treatment and thereafter, including subject's general condition, clinical signs and symptoms, any adverse events during discharge, medical physical examination, observation of injection site reactions and other adverse events, and otologic examinations. Otologic examinations include ear inflammation, ear infection, ear bleeding, pure tone test, speech recognition, ABR, DPOAE, vestibular assessment, etc. Laboratory tests include blood, urine, function of liver and kidney, blood electrolytes, coagulation. Monitor the occurrence of adverse events specially. The above contents include the safety indicators for RRG-003, aiming to control possible adverse drug reactions and risk factors during the trial.
- (2) Monitor and control possible adverse drug reactions and risk factors during the trial by signs and symptoms, laboratory tests, and otologic imaging; and give advice on handling.
- (3) The subject can withdraw from the trial at any time during any phase of the trial.

(4) The safety and efficacy data from this trial are regularly analyzed by the principal investigators and/or statisticians, who decide whether the trial should be continued.

(5) If the subject experiences an adverse event related to the investigational drug during the trial, the following principles need to be followed for handling of adverse event.

If an accident occurs during inner ear surgery, terminate injection promptly. And medical treatment should be conducted by the investigator;

Adverse events that do not meet the DLT during the observation of DLT are not treated generally;

After completion of DLT observation, adverse events should be handled actively;

Once adverse event happens in the subject, the investigator is responsible for making relevant medical decisions based on clinical practice to ensure that the subject is treated appropriately and the handling of AE should be documented.

(6) Risk of infection after inner ear drug administration

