## 15.2 Statistical analysis plan

Descriptive statistics are primarily used to analyze trial results. In general, measurement data will list the number of observational cases, mean, standard deviation, median, quartile, maximum and minimum. Enumeration data will list frequency and relative frequency. Unless otherwise specified, all of statistical tests will perform two-tailed test with a 95% confidence interval. Statistical analysis will be performed in a version of SAS 9.4 or higher version.

Use descriptive statistics to describe the number and proportion of subjects entering each analysis set, the number and proportion of subjects completing the trial and withdrawing consent, and the reasons for withdrawing consent (and proportion of subjects) for each dosage group; to describe the baseline characteristic of each dosage group.

Use the Safety Analysis Set to summarize treatment-emergent adverse event (TEAE) and adverse reaction for each dosage group; the AEs, occurs after signing informed consent and before treatment, will be only tabulated based on per subject and not summarized. TEAE is defined as the adverse event that is not present before dosing and occurs within 28 days (inclusive) after administration. The severity of adverse event and adverse reaction will be graded based on the NCI-CTCAE v5.0. Adverse event and adverse reaction will further be summarized based on System Organ Class and Preferred Term.

Using the safety analysis set baseline data, post-dosage data, and change from baseline were summarized for each follow-up visit and each dosage group, according to safety data such as laboratory, vital signs, electrocardiogram, physical examination, and otologic examination. Shift tables will be used to describe change from baseline after each follow-up visit to determine whether each examination result was normal and clinically significant as categorical data.

Use Per-Protocol Set to summarize efficacy data at each efficacy evaluation point and plot the efficacy-time curve of each subject, the mean efficacy-time curve of each dosage group, and the mean efficacy-curve of all subjects, according to efficacy data change from baseline in each dosage group.

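### For hearing thresholds, the section 15.2 safety shift tables are uninformative as written, because a qualifying ear starts in the worst category; no Safety Analysis Set output counts injected ears that lose hearing

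*Supplement*

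**What the plan says.** All references are to protocol v5.

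- **Section 15.2, numeric safety summary.** "baseline data, post-dosage data, and change from baseline were summarized for each follow-up visit and each dosage group". The population is the Safety Analysis Set, and otologic results are among the data types named. The general descriptive statistics include median, quartiles, minimum and maximum.
- **Section 15.2, shift tables.** "Shift tables will be used to describe change from baseline after each follow-up visit to determine whether each examination result was normal". The rest of that sentence makes clinical significance part of the same classification. No cut-offs are given. The plan does not say whether clinical significance is judged on the result or on the change.
- **Section 13.8.2, item (1).** "Otologic examinations include ear inflammation, ear infection, ear bleeding, pure tone test, speech recognition, ABR, DPOAE, vestibular assessment, etc". The same item describes these contents as including the product's safety indicators.
- **Sections 7.2 and 7.3.** The ear items listed for safety are "external ear and ear canal, tympanic membrane, tympanic chamber, mastoid process", plus vestibular function. Pure tone audiometry (PTA), ABR, ASSR and DPOAE appear under preliminary efficacy instead.
- **Section 4.1, item 13.** "Audiology inclusion criteria: Severe to complete hearing loss", set at 65 dB or worse. Test, frequency and ear are not named.
- **Sections 3.1, 11 and 13.2.** A grade 2 ear event, and so a DLT within 42 days, includes "Threshold shift >20 dB at 4 kHz in at least one ear". Grade 3 includes the same shift at 2 to below 4 kHz. Section 13.2 grades threshold shifts as ear adverse events. DLT at week 6 is the primary indicator.
- **Section 15.2, other outputs.** Treatment-emergent events are those starting within 28 days of dosing. Efficacy data, including a curve for each subject, are summarised on the Per-Protocol Set.
- **Section 20.** Otologic examination is scheduled at W2, W4, W6, W13, W26 and W52, and long-term safety is assessed at the last three.

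**The concern.** A shift table shows harm only when a result can move to a worse category. If hearing thresholds go into the section 15.2 shift tables, a qualifying ear begins as abnormal and, on any ordinary reading, clinically significant. No worse category is defined, so further loss leaves the ear in the same cell.

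This matters because the trial's primary purpose is safety and tolerability, and section 13.8.1 lists mild hearing loss among the ear reactions above 5% and unilateral deafness among those below 5%. A reader of the safety tables will want to know how many injected ears ended with less hearing than before dosing, or lost hearing they had regained. The shift table looks like the place for that answer and does not give it.

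**Working it through.** The plan states no figure to reproduce, so the check asks what each planned output would show.

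**1. Shift table.** I took three categories: normal, abnormal but not clinically significant, and abnormal and clinically significant. Assumptions, none of them in the documents: a normal cut-off of 20, 25 or 30 dB; a 10 dB band above it as not clinically significant; a test output limit *L* of 95, 100, 110 or 120 dB; 5 dB steps; and significance judged on the result. With *n* = (*L* − 65)/5 + 1 possible levels, there are *n*(*n* − 1)/2 worsening pairs. A shift of more than 20 dB needs at least five steps, which gives (*n* − 5)(*n* − 4)/2 pairs, and the baseline can be no higher than *L* − 25.

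| *L* (dB) | *n* | Worsening pairs | Pairs that change category (any cut-off) | Pairs with shift >20 dB | Highest baseline that can show >20 dB |
|---|---|---|---|---|---|
| 95 | 7 | 21 | 0 | 3 | 70 |
| 100 | 8 | 28 | 0 | 6 | 75 |
| 110 | 10 | 45 | 0 | 15 | 85 |
| 120 | 12 | 66 | 0 | 28 | 95 |

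The highest not-significant level is 30 + 10 = 40 dB, well below 65 dB, so the zeros do not depend on the exact cut-off. These are counts of possible pairs, not expected frequencies. An ear going from 65 to 95 dB stays in the worst category in the shift table, although it is a +30 dB change in the numeric summary.

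**2. Numeric change summary.** As an illustration, suppose six injected ears, of which five improve by 40 dB and one worsens by 25 dB. The mean improvement is (5 × 40 − 25)/6 = 175/6 = 29.2 dB. The group extreme would show the 25 dB worsening, but not how many ears worsened, in which child, or whether the ear was injected.

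**3. Gain followed by loss.** The stated reference is the pre-dose value. An ear that gains 40 dB and then loses 25 dB still reads as 40 − 25 = 15 dB better than baseline. No Safety Analysis Set output compares it with its own best post-dose value.

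**4. Event windows.** A loss starting on days 29 to 42 is outside the treatment-emergent summary but inside the DLT window. Section 15 plans no DLT table. After day 42 it is outside both windows, and W13 is day 13 × 7 = 91. Section 13.5 would still have it recorded as an adverse event, and it could enter the adverse-reaction summary if judged drug-related. Those summaries are by dosage group and are not specified by ear.

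**5. Sections 7.2/7.3 against 13.8.2.** If 13.8.2 governs, thresholds enter a shift table that does not register their loss. If 7.2 and 7.3 govern, thresholds are efficacy data and may be summarised only on the Per-Protocol Set. Neither reading gives a Safety Analysis Set count of injected ears that worsened.

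**The case against.** The strongest reply is that hearing loss is already captured elsewhere. A shift of more than 20 dB at the named frequencies is a DLT within 42 days and a gradable adverse event, adverse events are tabulated in the Safety Analysis Set, and change from baseline is summarised with minimum and maximum. Each subject also gets a curve over time. With 4 to 12 effective cases (section 5), someone could read every curve, and a gain followed by a loss would show on it.

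Much of this stands. A reader might infer that lost hearing never appears, or that the safety outputs cannot record it. The documents do not support that: early loss has defined routes into the report, and the curves and extremes give partial sight of later loss. A reader might also extend the point to all otologic results. That fails too, because infection, inflammation, bleeding and vestibular findings can move from normal to abnormal, and nothing requires DPOAE to be abnormal at entry. Nor is 'never' safe for thresholds, since significance judged on the change would let a loss be marked.

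What the reply does not supply is a count. The curves are per subject, although section 3 allows bilateral dosing, and they use the Per-Protocol Set, which requires protocol compliance. A child whose administration was not completed as planned could be left out. The event windows close before W13.

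**Conclusion.** The point holds for hearing thresholds: PTA, ABR, and ASSR if it is treated as an otologic safety test (section 13.8.2 does not name it). For these the shift tables are uninformative as written, and no planned Safety Analysis Set output counts injected ears that lose hearing. The gap is widest at W13 to W52.

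Severity is minor to moderate. A reader might infer that a shift table without movement would be taken as proof of no harm, or that hearing loss is the treatment's chief local risk. The documents establish neither: other outputs would sit beside the table, and section 13.8.1 lists hearing loss as one reaction among many.

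The conclusion assumes that clinical significance is judged on the result and that the tabulated ear and frequency meet the 65 dB criterion. The v5 visit grid is not legible for the hearing tests, so the late visits are taken from section 20.

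**What to change.** In section 15.2:

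1. State that hearing thresholds are summarised as safety data in the Safety Analysis Set, and reconcile sections 7.2 and 7.3 with 13.8.2. Say whether ASSR is included.
2. For thresholds only, replace the normal/abnormal shift with ordered dB bands plus a 'no response' level. Cross-tabulate per ear, pre-dose against each visit and against the worst post-dose value, separately for injected and uninjected ears. Keep the existing shift table for the other otologic findings.
3. Add the number of injected ears more than 20 dB worse than pre-dose (the shift size already in section 3.1) and the number more than 20 dB worse than their own best post-dose value, with a per-ear listing.
4. Note beside the counts that an ear at the test's output limit cannot show loss from pre-dose, and that one less than 25 dB below it cannot reach the 20 dB criterion on 5 dB steps. Comparison with the best post-dose value can still detect a lost gain there.

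The cost is some SAP wording and a little more table work on data already planned. No new test or visit is needed.

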### **4.3 Suspension criteria**

6. Unsuccessful administration. Drug administration was not completed according to the protocol.
7. The participants withdraw from the test or loss of follow-up
8. Allergic reaction or serious adverse events. Due to the obvious abnormalities of drug safety related laboratory indicators or adverse events (such as severe allergic reactions) during administration process, the investigator and/or the sponsor considers that it is not appropriate to continue injecting drugs based on ethical consideration. People who need rescue due to serious adverse events. Complicated by other serious diseases during the trial period, and the investigator judges that it is not appropriate to continue to participate in the trial;
9. During the 6-week evaluation period, the original condition progresses or other treatments are required: if no treatment measures are taken temporarily, they can continue to participate in the trial or withdraw from the trial at the discretion of the investigator; if other treatments are required, the trial should be withdrawn;
10. Serious violation of trial protocol. The participants or the participants' guardian refused to

follow-up or keep serum samples, and the combined use of prohibited drugs that significantly exceeds the dosage may bring risks; the required inspection items are not complete as planned, resulting in an inability to assess safety and efficacy; the informed consent process is incomplete or there is no informed consent procedure; the participant's guardian did not sign the informed consent or temporarily withdrew the informed consent.

The original data and documents of the selected or enrolled subjects should retain for retention and intentionality analysis (ITT), whether they drop out or not.

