#### **15. Statistical analysis plan, definition and selection of statistical analysis data set**

##### **15.1 Definition and selection of analysis data set**

Enrolled Patients Set (EPS): defined as all enrolled cases, with or without investigational drug. The data set is used to analyze data such as demography and baseline information, subject allocation, and protocol violation.

Safety Analysis Set (SAS): defined as all enrolled cases that use the investigational drug at least once. The data set is used to analyze safety data.

Efficacy Evaluable Analysis Set (EEAS): defined as all enrolled cases who had at least one efficacy assessment after receiving investigational drug. The dataset is used for analysis of preliminary efficacy data.

Full Analysis Set (FAS): Defined as all enrolled cases who receive investigational drug at least once and have at least one post-baseline efficacy assessment according to the intention-to-treat (ITT) principle. The dataset is used for efficacy analysis.

Per-Protocol Set (PPS): defined as all cases, incorporated in the full analysis set, who comply with the protocol, have good medication adherence, do not use prohibited drugs during the trial, and have a defined efficacy assessment in the trial. The dataset is used for efficacy analysis.

Statistical analysis methods

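### Section 15.2 (v5) names only the Per-Protocol Set for the efficacy summaries and curves, in conflict with 15.1 and 4.3, so the reported hearing gain may be overstated

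*Supplement*

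**What the plan says.** All references are to protocol v5, whose Section 15 is the final analysis plan.

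- **Section 15.1** gives three sets a role in efficacy. The EEAS takes enrolled children with an efficacy assessment after dosing: "The dataset is used for analysis of preliminary efficacy data". The FAS is limited to dosed children, and its definition ends: "once and have at least one post-baseline efficacy assessment according to the intention-to-treat (ITT) principle. The dataset is used for efficacy analysis". The PPS is the part of the FAS that meets these conditions: "comply with the protocol, have good medication adherence, do not use prohibited drugs during the trial, and have a defined efficacy assessment in the trial".
- **Section 15.2** then names one set in its efficacy paragraph: "Use Per-Protocol Set to summarize efficacy data at each efficacy evaluation point". The same sentence covers each child's efficacy-time curve, the mean curve per dose group, and a mean curve said to be for all subjects. The only use it gives to the FAS and EEAS is to count who enters each set.
- **Section 4.3** covers the case where "During the 6-week evaluation period, the original condition progresses or other treatments are required". An untreated child may stay at the investigator's discretion, but "if other treatments are required, the trial should be withdrawn". It closes by saying that the data of selected or enrolled children "should retain for retention and intentionality analysis (ITT), whether they drop out or not".

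**The concern.** A plan that defines an intention-to-treat set for efficacy and promises to keep dropouts for it should produce an efficacy result on it. Section 15.2 plans none. A mean curve described as covering all subjects but drawn from the PPS is also mislabelled.

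The choice matters because PPS membership is settled by what happens after dosing. A child who needs other treatment in the 6-week period, whose administration is incomplete, or who misses required tests meets a suspension criterion in 4.3 and is then likely to fail the PPS conditions. At least the first of these may be related to a poor result. There is one arm, so no comparator would show a similar loss, and with so few children one exclusion is visible in a mean or a proportion.

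Efficacy is not the primary question, but it is used. Section 13.8.2 has safety and efficacy data reviewed regularly to decide whether the trial continues. Section 3 ties expansion of dose groups to risk and benefit. The amendment summary cites hearing recovery as a reason for enlarging the trial.

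**Working it through.** **Text check.** Side by side, the passages do not agree:

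| Section | Set linked to efficacy |
|---|---|
| 15.1 | EEAS, FAS and PPS, with no statement of which is main |
| 15.2, efficacy paragraph | PPS only, for summaries and all curves |
| 4.3, closing sentence | Data retained for intention-to-treat, dropouts included |
| 15.2, safety paragraph | Safety Analysis Set (SAS): change from baseline at each visit, otologic examination included |

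The last row matters. Section 13.8.2, item (1), counts pure tone testing, speech recognition, ABR and DPOAE among the otologic examinations. On that reading, some hearing measures would also be tabulated for all dosed children under the safety heading. ASSR is not named there, and no curve is planned on the SAS.

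**Size.** The plan has no figure to reproduce: Section 5 gives 4-12 effective cases without a response rate, standard deviation or dropout rate. What follows is an illustration.

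Inputs:
- N, children dosed: 4 and 12, the limits in Section 5. That section counts effective cases (dosed per protocol, observed at least 6 weeks), so using them as numbers dosed is an assumption.
- k, dosed children outside the PPS: 1 to 3, assumed.
- r, responders within the PPS: all N − k of them, assumed.

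Formulas: PPS rate = r/(N − k). All-dosed rate = r/N if the excluded children do not respond, and (r + k)/N if they do. Intervals are exact (Clopper-Pearson) 95%.

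| N | k | PPS rate | All dosed, excluded do not respond | Gap (points) |
|---|---|---|---|---|
| 12 | 1 | 11/11 = 100% (71.5-100) | 11/12 = 91.7% (61.5-99.8) | 8.3 |
| 12 | 2 | 10/10 = 100% (69.2-100) | 10/12 = 83.3% (51.6-97.9) | 16.7 |
| 12 | 3 | 9/9 = 100% (66.4-100) | 9/12 = 75.0% (42.8-94.5) | 25.0 |
| 4 | 1 | 3/3 = 100% (29.2-100) | 3/4 = 75.0% (19.4-99.4) | 25.0 |
| 4 | 2 | 2/2 = 100% (15.8-100) | 2/4 = 50.0% (6.8-93.2) | 50.0 |

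If the excluded children respond, every all-dosed rate in the table becomes 100% and the gap is zero. If one PPS child fails to respond and the excluded child does respond, the sign reverses: with N = 12 and k = 1, the PPS gives 10/11 = 90.9% and all dosed gives 11/12 = 91.7%.

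Section 15.2 plans changes from baseline rather than proportions, so the same check on a mean is closer to its outputs. Assume a PPS mean gain of 40 dB and 0 dB in the excluded children. The mean over all N is 40 × (N − k)/N: 36.7 dB (N = 12, k = 1), 33.3 dB (12, 2), 30 dB (4, 1) and 20 dB (4, 2).

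**The case against.** The strongest reply has four parts.

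1. **The PPS is not the only set on which hearing is reported.** The SAS tables of otologic examinations may hold pure tone, speech, ABR and DPOAE changes for every dosed child. A reader might infer from the efficacy paragraph that no hearing result covers all dosed children. The text does not support that. It does support saying that the results labelled as efficacy, all the curves, and ASSR rest on the PPS.
2. **Overstatement is not established.** A reader might also infer that response will be inflated. That depends on who is excluded. Incomplete administration, missed tests, consent faults or refusal of serum samples need not relate to hearing outcome. The rule on other treatment applies within the 6-week period, whereas Section 20 places preliminary efficacy at weeks 13, 26 and 52. Section 4.3 does not say that other treatment means hearing treatment, and the PPS definition does not name withdrawal; that link runs through protocol compliance and the need for a defined assessment. An upward bias is plausible, not certain.
3. **Efficacy is secondary and mainly descriptive.** The primary indicator is dose-limiting toxicity at week 6, safety uses the SAS, and no efficacy test or success threshold depends on the set.
4. **Exclusions would be countable.** Section 15.2 reports numbers entering each set, and 15.1 has protocol violations analysed on all enrolled children.

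All four stand as limits on strength. None says which set is main, and none gives the curve for all subjects a basis that matches its label. A count of exclusions also does not show how the excluded children fared.

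**Conclusion.** The conflict between 15.2 on one side and 15.1 and 4.3 on the other is plain from the text. Followed as written, 15.2 can leave treated children out of the efficacy summaries and curves of a very small single-arm trial, for reasons that may be linked to outcome. The reported gain may therefore be too favourable.

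The size cannot be derived from the documents. The range of 8 to 50 points holds only under the assumptions above: all PPS children respond, no excluded child does, and 1 of 12 to 2 of 4 dosed children are excluded. It also uses a responder proportion that 15.2 does not plan; Section 11 calls a threshold change clinically significant only for pure tone audiometry. Because the primary safety analysis is unaffected, this is a point that should be fixed before analysis, not one that undermines the trial's main purpose.

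**What to change.** In Section 15.2:

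- Make the FAS the main set for the efficacy summaries and all efficacy curves, and merge it with the EEAS, which is nearly identical as defined.
- Keep the PPS as a sensitivity summary.
- List every dosed child, with the reason for any exclusion. Include children without a post-baseline efficacy assessment: the FAS requires one, so a child who leaves before it is lost from the FAS as well as the PPS, and changing sets alone does not recover that child.
- If a responder count is reported, use all dosed children (SAS) as the denominator.

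Counting every child who leaves as a non-responder is one option among several. The plan gives no responder definition to support it, so it is not asked for here.

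The cost is a change of wording in the analysis plan and one more set of tables. No further data or participants are needed. The headline efficacy result may look less favourable.
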